**Methods:**

A randomised placebo-controlled clinical trial with a 2 × 2 factorial design will evaluate the clinical efficacy, cost-effectiveness and recurrence rates of adding physiotherapy to an injection. In addition, the clinical efficacy and adverse effects of corticosteroid injection beyond that of a placebo saline injection will be studied. 132 participants with a diagnosis of lateral epicondylalgia will be randomly assigned by concealed allocation to one of four treatment groups – corticosteroid injection, saline injection, corticosteroid injection with physiotherapy or saline injection with physiotherapy. Physiotherapy will comprise 8 sessions of elbow manipulation and exercise over an 8 week period. Blinded follow-up assessments will be conducted at baseline, 4, 8, 12, 26 and 52 weeks after randomisation. The primary outcome will be a participant rating of global improvement, from which measures of success and recurrence will be derived. Analyses will be conducted on an intention-to-treat basis using linear mixed and logistic regression models. Healthcare costs will be collected from a societal perspective, and along with willingness-to-pay and quality of life data will facilitate cost-effectiveness and cost-benefit analyses.

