### Injection

A routine clinical examination will be conducted by the treating medical practitioner prior to injection of either (1) 1 ml Triamcinolone Acetonide (10 mg/ml) (Kenacort-A 10) with 1 ml Lignocaine (1%) [Corticosteroid injection] or (2) 0.5 ml Isotonic Saline (0.9%) [Saline injection]. Injection will be administered into the most palpably tender point(s) in the region of the lateral epicondyle, consistent with previous studies [10,16,19,20]. The syringe will be drawn up and administered with the participant unable to view its contents to facilitate participant blinding. In addition, standardised post-injection information will be provided verbally and in the form of a printed pamphlet based on published recommendations [10,16,21]. Rest from all strenuous activity for 1–2 weeks following injection will be strongly recommended, followed by gradual return to normal activities. Participants will be instructed to avoid aggressive return to activities even if substantial relief is obtained, to minimise potential recurrence of their symptoms. All participants will be warned of normal post-injection responses and to inform their doctor if there is any suggestion of infection or other adverse events. All adverse reactions will be managed by a committee chaired by the chief investigator (BV).

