#### Recurrence

Recurrence will primarily be defined as occurring when a participant rates a success at 4 or 8 weeks and a no-success beyond 8 weeks on the global perceived improvement scale [10]. This definition of recurrence which evaluates the pattern of recurrent events over time has been used in previous studies of LE [10,20,38]. In addition, participants will be questioned using a semi-structured interview at 12, 26 and 52 weeks about their experience of symptom aggravation and possible reasons for their recurrence. This data will enable better understanding of recurrences and best practice measurement of recurrence rates in future analyses and trials.

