#### Adverse events

All adverse events, defined as any negative or unwanted reactions to intervention, will be recorded. These will include pain (lasting longer than 7 days), skin pigmentation changes, subcutaneous atrophy or any other reported physical discomfort. As well as the adverse effects committee (chaired by BV) that will manage adverse reactions at the time of the adverse reaction, we will administer a questionnaire at 8 and 52 weeks to record all such patient identified events. This will capture additional ill effects not reported at the time of their occurrence. These are likely to be minor aggravations in symptoms. The questionnaire will use open-ended questions and will be placed in a sealed envelope to be opened by a research assistant not involved in outcome measurement. The intervention-specific incidence of each adverse event will be computed.

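### The adverse-event questionnaire is open-ended, so it does not ensure that every participant is asked about the three named reactions or how long pain lasted

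*Protocol article*

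**What the plan says.** The abstract of the protocol article makes harm an object of study: "the clinical efficacy and adverse effects of corticosteroid injection beyond that of a placebo saline injection will be studied".

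The Adverse events section (under Secondary outcome measures) sets a broad definition, "All adverse events, defined as any negative or unwanted reactions to intervention, will be recorded", and then lists what is covered: "These will include pain (lasting longer than 7 days), skin pigmentation changes, subcutaneous atrophy or any other reported physical discomfort". It closes by promising an incidence of each event by intervention.

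Events are to be managed by a committee when they arise. In addition, "we will administer a questionnaire at 8 and 52 weeks to record all such patient identified events". The purpose is supplementary: "This will capture additional ill effects not reported at the time of their occurrence". The format is fixed: "The questionnaire will use open-ended questions and will be placed in a sealed envelope". The authors expect mostly small symptom flares from this source.

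Three other places bear on collection:

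- **Injection section:** participants are told "to inform their doctor if there is any suggestion of infection or other adverse events".
- **Table 2:** the adverse-events row is marked in the column for 4, 8, 12, 26 and 52 weeks, with no method given.
- **Recurrence section:** "participants will be questioned using a semi-structured interview at 12, 26 and 52 weeks about their experience of symptom aggravation".

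**The concern.** The planned output and the described instrument do not match. An incidence for a named reaction needs a numerator found in the same way in everyone and a denominator of people who were asked. An open question gives neither by design. A participant with a pale patch or a dent near the elbow may not connect it with the injection, and silence is then counted as absence.

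For pain the gap is sharper. The plan's own case definition needs a duration above 7 days, and nothing described collects duration. A reply such as 'it was sore afterwards' cannot be classified.

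At stake is the comparison of corticosteroid with saline on harm. If some named reactions go unrecorded, both incidences fall, the absolute difference narrows, and a real excess is harder to see.

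**Working it through.** **Step 1. Does any described route ask everyone about each named reaction?**

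| Route | When | Asks each participant about skin change? | Collects pain duration? |
|---|---|---|---|
| Report to the doctor (Injection) | As events occur | Left to the participant | Not stated |
| Questionnaire (Adverse events) | 8 and 52 weeks | Not ensured: open-ended | Not ensured |
| Semi-structured interview (Recurrence) | 12, 26, 52 weeks | No: concerns aggravation and recurrence | Not stated |
| Table 2 row | 4, 8, 12, 26, 52 weeks | Method not given | Method not given |

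No section mentions a checklist, a direct question on the named reactions or a skin examination. The gap therefore stands on the text.

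**Step 2. Are the collection times consistent?** Table 2 marks five follow-ups and the Adverse events section gives two questionnaire times. Either another, undescribed collection takes place at 4, 12 and 26 weeks, or the two places disagree.

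**Step 3. What would incomplete capture do?** The plan gives no adverse-event figure to reproduce, so this is algebra followed by an illustration.

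Let the true risks be p1 (steroid) and p0 (saline), with the same capture share c in both groups.

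- Recorded difference = c × (p1 − p0), which shrinks in proportion to c.
- Recorded relative risk = (c × p1)/(c × p0) = p1/p0, which is unchanged in expectation.

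Assumptions, none of them from the documents: p0 = 2%; p1 = 10%, 15% or 20%; c = 0.9 or 0.5. Group size is 132/2 = 66 per injection level, taking equal allocation and no loss. Power is by exact enumeration of Fisher's two-sided test at 0.05.

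| True steroid risk | Recorded difference, c = 0.9 | Recorded difference, c = 0.5 | Power, c = 0.9 | Power, c = 0.5 |
|---|---|---|---|---|
| 10% | 0.9 × 8 = 7.2 points | 0.5 × 8 = 4.0 points | 0.272 | 0.064 |
| 15% | 0.9 × 13 = 11.7 points | 0.5 × 13 = 6.5 points | 0.632 | 0.237 |
| 20% | 0.9 × 18 = 16.2 points | 0.5 × 18 = 9.0 points | 0.871 | 0.470 |

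At a 15% true risk, expected recorded steroid cases are 66 × 0.15 × 0.9 = 8.9 against 66 × 0.15 × 0.5 = 5.0. The relative risk stays at 13.5/1.8 = 7.5/1.0 = 7.5.

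The choice of test matters too. A normal approximation for 15% against 2% gives power 0.77 at full capture and 0.46 at half. If the 0.01 level in Planned Data analysis were applied to harms, the Fisher figures in the 15% row would be 0.394 and 0.071.

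**The case against.** The strongest case against the point has four parts.

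- **The questionnaire is a back-up.** Events are also reported as they occur, participants receive verbal and printed post-injection information, and Table 2 schedules adverse events at every follow-up. A reader might infer that the questionnaire is the only solicited collection. Table 2 does not allow that: it is only the one instrument whose format is described. This part stands.
- **Open-ended describes the form of the answer, not necessarily the topic.** A question about skin changes near the injection and how long they lasted would be open-ended and still targeted. The form is not shown, and an article may condense its wording. This stands in part: it rules out saying that the form cannot yield the incidences. It does not remove the point, because the article states the format as a choice and nothing in it ensures direct questions on the named reactions.
- **Under-recording is not shown.** A reader might infer that these events will be under-recorded and the steroid comparison weakened by the amounts tabulated. The documents give no event rate and no capture share. Nothing ties 50% capture to this questionnaire, and the plan promises incidences for harms, not a Fisher test at 0.05. This stands.
- **Blinding protects the comparison.** Participants and assessor are blind to injection content, so no stated reason exists for capture to differ between injection groups, and equal capture leaves the expected relative risk unchanged. This stands for the ratio. It does not help the incidences or the absolute difference. Between the physiotherapy levels the chance to report may differ, because one level has eight extra practitioner sessions.

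Open questioning is a legitimate method, but the plan need not choose: both kinds of question can be asked, open first.

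**Conclusion.** The concern holds in a limited form. The plan names three reactions, attaches a duration rule to one and promises an incidence for each event, yet no described route ensures that every participant is asked about each reaction or about duration. Non-mention cannot be told from absence, the 7-day rule may not be applicable, and the incidences and absolute differences may be understated.

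The size cannot be derived from the documents. The illustration shows only that, under the assumed risks and equal capture, a fall in capture from 90% to 50% would cost much of the power to see a harm while leaving the expected relative risk where it was. It is not an estimate of what this questionnaire would miss.

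The difference in timing between Table 2 and the Adverse events section is a separate, smaller defect. The remedy is cheap and harm is an object of study, so the change should be made.

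**What to change.** 1. Keep the open-ended question first. Then add one direct item for each named reaction: skin colour change, skin thinning or a dent, and pain after the injection with its start and duration in days.
2. Use identical wording in all four arms and keep the same sealed-envelope handling.
3. Have the questionnaire completed after the global improvement rating and after the question on injection content at that visit, so that the items cue neither the primary outcome nor the blinding check, which is also due at 8 and 52 weeks.
4. Report open-elicited and prompted events separately, with the number asked as the denominator for prompted events.
5. Reconcile the collection times: either state what is collected, and how, at 4, 12 and 26 weeks, or align Table 2 with the Adverse events section.

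The cost is three items on a questionnaire that is already administered, with no extra visit or staff. The downsides are more minor events counted in every arm, rates less comparable with studies that used open questions only, and some possible cueing about injection content at later assessments. Separate reporting handles the comparability problem. The order of completion limits the cueing at that visit but cannot remove it for later ones.

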### Randomisation and allocation

Participants will be randomly allocated to groups by concealed allocation. The Queensland Clinical Trials Centre, an independent off-site body, will be responsible for generating the computerised randomisation schedule. An independent research officer will administer the schedule and perform all communication between participants and treating practitioners. Randomisation will be stratified according to baseline pain severity, as it has been found to be a strong prognostic indicator for LE [54]. The mean VAS pain score reported in a previous clinical trial (57.5 mm) [10] will be used to classify participants into high and low baseline pain.

### Sample size

The primary aim of this project is to detect a clinically important difference between injection alone and physiotherapy plus injection. It is estimated that 120 participants will be required to detect a 25% difference between physiotherapy and no physiotherapy (α = 0.05, β = 0.2), assuming a success rate of 27% in the least significant group. This difference is based on previous work and is clinically meaningful [20]. An extra 10% will be recruited to allow for conservative loss to follow-up, bringing the total participants to 132. The power calculation is based on previous findings that injection and physiotherapy are both effective interventions [10,20] and that the combination of the two will be additive, but not synergistic in effect.

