### Planned Data analysis

#### Clinical Efficacy

All analyses will be conducted on an intention to treat basis by an investigator who is blind to group allocation. The outcomes measured at 4, 8, 12, 26 and 52 weeks will be used to generate efficacy and recurrence indices that will be analysed using linear mixed and logistic regression models [10]. Baseline scores for each dependent variable will be entered as a covariate, relevant participant characteristics entered as a random effect and treatment conditions and time as fixed factors. Variables such as age, gender, duration of condition, nature of employment will be included as covariates in the analysis, if found to significantly influence outcomes over time. Regression diagnostics will be used to check for normality of the measures and homogeneity of variance where appropriate. Alpha will be set at 0.01 to compensate for the possible increase in type I error rates that may result from multiple testing. The dichotomous measures of success and recurrence will be analysed using relative risk, and numbers needed to treat in order to provide a meaningful indicator of treatment efficacy to practitioners.

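### The trial is sized at alpha 0.05, but the analysis section sets alpha at 0.01 without exempting the primary comparison; at 0.01 the planned sample gives about 60% power, not 80%

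*Protocol article*

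**What the plan says.** The Sample size section of the protocol names the comparison of injection alone with physiotherapy plus injection as the primary aim. It states that "120 participants will be required to detect a 25% difference between physiotherapy and no physiotherapy (α = 0.05, β = 0.2"). The lower of the two rates enters the calculation as a separate premise, worded as "assuming a success rate of 27% in the least significant group". A margin for attrition comes on top of this: "An extra 10% will be recruited to allow for conservative loss to follow-up, bringing the total participants to 132". The section assumes that the effects of the two factors add without synergy, so the comparison is between the two levels of the physiotherapy factor.

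The abstract describes the outcome behind these rates: "The primary outcome will be a participant rating of global improvement, from which measures of success and recurrence will be derived". The Success section defines success as the top two categories of that rating.

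The Clinical Efficacy section, under Planned Data analysis, covers all analyses, including the efficacy and recurrence indices, and names success and recurrence. It says: "Alpha will be set at 0.01 to compensate for the possible increase in type I error rates that may result from multiple testing". It does not confine the 0.01 level to secondary outcomes or additional time points, and it does not exempt the powered comparison.

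**The concern.** The significance level is an input to the sample size. A trial sized at 0.05 and tested at 0.01 keeps its participants but loses power, so the 80% in the Sample size section does not describe the test that the Clinical Efficacy section prescribes.

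Two things are at stake. First, the probability of detecting the difference that the protocol itself calls clinically meaningful is lower than stated. The Background criticises an earlier study of the same combination for a high type II error rate, so this matters on the protocol's own terms. Second, the decision rule for the main result is ambiguous. If the physiotherapy comparison gives a p-value between 0.01 and 0.05, one section supports calling it positive and the other negative. That choice should not remain open once the data are known.

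**Working it through.** **Inputs from the Sample size section**
- Lower success rate p1 = 0.27; difference 0.25, so p2 = 0.52.
- "α = 0.05, β = 0.2", that is, 80% power.
- 120 evaluable, 132 recruited.

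**Input from the Clinical Efficacy section**
- Analysis alpha 0.01.

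**Assumptions, not stated in the protocol**
- A two-sided test.
- Equal allocation, so 60 evaluable (66 recruited) per level of the physiotherapy factor.
- An unadjusted comparison of two proportions.
- 27% taken as the rate for the whole no-physiotherapy level.

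**Step 1: reproduce the planned number.** With mean rate (0.27 + 0.52)/2 = 0.395:
- s0 = √(2 × 0.395 × 0.605) = 0.6913
- s1 = √(0.27 × 0.73 + 0.52 × 0.48) = 0.6684
- n per level = [(z for alpha × s0 + 0.8416 × s1)/0.25]²

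At two-sided 0.05 (z = 1.960), n = 58.8, rounded up to 59 per level or 118 in total. This agrees with the stated 120, and the arcsine formula also gives 118. A one-sided test would need only 94, or 108 with continuity correction. A two-sided test with continuity correction would need 134. The two-sided, uncorrected version is therefore the natural reading.

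**Step 2: power with 60 per level.** Power = Φ[(0.25 × √n − z × s0)/s1].
- Alpha 0.05: (1.936 − 1.355)/0.6684 = 0.870, power 80.8%. Exact enumeration of the uncorrected chi-square test gives 81.1%.
- Alpha 0.01 (z = 2.576): (1.936 − 1.781)/0.6684 = 0.233, power 59.2%. Exact enumeration gives 60.8%.

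The risk of missing a true 25-point difference thus rises from about 19% to 39–41%.

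**Step 3: no loss to follow-up (66 per level), alpha 0.01.** (2.031 − 1.781)/0.6684 = 0.374, power 64.6%; exact 65.3%.

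**Step 4: what 0.01 would require.**
- For 80% power at 25 points: n = 87.9, rounded up to 88 per level, or 176 evaluable.
- With 60 per level: solving the power formula for the difference, with 27% in the lower group, gives about 30 points.

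**Step 5: sensitivity at alpha 0.01, 120 evaluable.**

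| Variant | Power |
|---|---|
| Arcsine formula | 60.3% |
| Unpooled variance | 62.6% |
| Fisher exact or continuity-corrected test | 53–54% |
| One-sided 0.01 | 68.8% |
| No-physiotherapy rate anywhere from 27% to 50%, difference 25 points | 57–60% |

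No variant reaches 80%.

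**The case against.** The best defence is that 0.01 was never meant for the powered comparison. The reason given for it is multiple testing, which fits the many outcomes and time points better than a single primary test. That may well have been the intention, but the text does not say so, and one sentence would settle it. Nor can the matter be left to an analysis plan that is not shown: the protocol fixes both levels itself, and they disagree.

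A second objection is that the 59–61% figure describes an unadjusted test, whereas the protocol plans logistic and mixed models with covariates and stratifies randomisation on baseline pain, which it regards as strongly prognostic. This stands as a qualification. Adjusted power cannot be computed from the document, and the Sample size section claims no gain from adjustment. Likewise, the 27% may refer to the lowest of the four cells rather than to the whole no-physiotherapy level, but the last row of the sensitivity table shows that this changes little.

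A reader might also go further than the documents allow in three ways:
- **That a real benefit would probably be reported as no difference.** At about 60% power, detecting a true 25-point difference remains the likelier result.
- **That the sample-size arithmetic is wrong.** It reproduces; the fault is an inconsistency between two sections.
- **That 0.01 leaves a particular family-wise error rate.** The protocol does not fix the number of tests. The outcomes are also plainly dependent: success is the global rating dichotomised, recurrence is built from success over time, and the same participants are followed throughout. A figure that treats the tests as independent would not be sound.

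**Conclusion.** The concern holds as an inconsistency between the Sample size and Clinical Efficacy sections. The stated 80% power belongs to a test at 0.05; the decision rule as written is 0.01, with no exemption for the primary comparison. At that level the planned 120 evaluable participants give about 59–61% power for 27% against 52%, or about 65% if all 132 are retained, and 80% power is reached only for a difference of about 30 points.

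These figures rest on a two-sided, unadjusted two-proportion test, equal allocation and 27% as the no-physiotherapy rate. The protocol states none of the first three, and its wording leaves the fourth open; together they reproduce its own sample size. The exact percentage would shift under other assumptions, but every variant tried stays well below 80%. Because the conflict governs both the stated power and the success criterion for the primary comparison, it needs to be resolved.

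**What to change.** Reconcile the two sections before unblinding, in one of two ways.

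1. **Reserve 0.05 for one test.** State that a single pre-specified primary test, the physiotherapy main effect on success, is made at two-sided alpha 0.05, and that 0.01 applies to all other outcomes, all other time points and the injection factor. The time point has to be named. The Sample size section gives none, nor does it state that the test is two-sided, so both would be new text. The 52-week assessment, which the Outcome assessment section names as the primary end point for long-term effects, is one candidate.
2. **Keep 0.01 for the primary test.** Restate the Sample size section as giving about 60% power for a 25-point difference, or 80% power for about 30 points, with 120 evaluable participants.

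Either option costs about two sentences and no additional participants. The drawback of the first is that one outcome and one time point are singled out; the drawback of the second is a less favourable power statement.
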